#### Monthly Surveys

Participants are prompted via text or email to complete monthly surveys to track their alcohol consumption for 6 months after randomization. A TLFB survey asks participants to report the number of standard drinks consumed in the last 30 days, with the option to specify the event (vacation, birthday, holiday, wedding, sports, party, travel, stress, or other). Participants are sent up to 3 reminders to complete the monthly TLFB and have a total of 14 days to complete the survey.

#### Baseline and Quarterly Surveys

During months 0 (baseline), 3, and 6, participants are prompted to complete a series of surveys sent as a text or email. Participants have a 30-day window to complete the surveys for compensation.

#### Connections Use

Connections app usage will be recorded automatically in server log files and collected continuously during the 6-month intervention. Use is defined as patients accessing Connections and going beyond the home page. The study team will examine the number of days on which patients use the app and the mean number of pages used beyond the home page.

#### Qualitative Data Collection

To explore barriers and facilitators to successful implementation of the Connections app at the patient, provider, and clinic levels, qualitative interviews will be conducted with key stakeholders about their perspectives on the implementation process. A qualitative researcher experienced in mHealth apps will conduct interviews. Semistructured interview guides will include questions based on the domains of the National Academy of Engineering’s (2005) multilevel model of system changes, as well as more open-ended questions designed to probe the participants’ own experiences and opinions [54]. Data collection and analysis for assessing the implementability of the Connections app will happen in years 3-5 at the conclusion of the active intervention.

A total of 30 patients from both Wisconsin and Michigan will be interviewed: 15 who used the Connections app extensively during the intervention (ie, from the top quartile based on overall use) and 15 who did not (from the bottom quartile). Participants will be purposively sampled from these strata to ensure a balanced sample for sex and multidisciplinary ALD clinic vs general hepatology-only clinic attendance, as these are 2 hypothesized key moderators of effect. Patients will be asked about the ease of use and acceptability of the content, features, and functioning of the Connections app, their overall experience with learning about the app, and suggestions for improving how the clinic introduces patients to the app and provides ongoing support for its use.

Additional interviews will be conducted with clinic staff and study coordinators to gather information about the implementation process. Realms for exploration will include the following: (1) What types of workflow and process changes were needed to maximize the adoption of the Connections app in the clinical setting? (2) What helped staff to implement these changes? Providers and staff will also be asked about their observations of any differences in app adoption and use between patient categories or characteristics, and about theoretical challenges with implementing an app like this in clinic.

The research team will debrief after early interviews and make any needed modifications to the interview guides. Interviews will be audio-recorded via secure web platform such as Zoom or similar (version 5.11.3).

### Data Analysis

#### Primary Analysis

To test the primary aim, alcohol consumption outcomes will be compared between the usual care condition and the usual care plus the Connections app condition, stratified by site and clinic type, and adjusting for baseline abstinence and risky drinking (AUDIT-10 score). The analysis will use an intent-to-treat paradigm and use longitudinal linear mixed-effects models. The analyses will test a group-by-time interaction on the outcomes. If the interaction is not significant, a main group effect will be examined. The analysis assesses direct treatment effects on patient outcomes over time. The research team will construct a longitudinal model of our outcome measures at baseline and at 3 and 6 months after randomization. To address potential incomplete data from individual subjects, the research team will also conduct a mixed-model analysis of repeated measures based on the general linear model with an assessment of various covariance structures (compound symmetric, autoregressive order one, and unstructured). Covariance structure selection will be based on Akaike’s information criterion and Schwarz’s Bayesian criterion [55,56]. Pairwise comparisons between treatment groups and specific treatment time contrast in the mixed model will be conducted to respond to between-group effects and time-based effects. To address issues of incomplete data, the research team plans to estimate treatment effects according to four approaches: intention-to-treat, as-treated, per-protocol, and complier-average causal effect. Secondary analyses (as-treated, per-protocol, CACE) will only be formally evaluated if the primary intention-to-treat outcome demonstrates a statistically significant effect. Details of these approaches are outlined in Little and Yau [57] and Jo [58]. Missing data patterns (eg, possible dropouts) will be established from the longitudinal data and will be used to adjust the longitudinal intervention analysis according to pattern-mixture modeling. The research team will also examine additional secondary hypotheses (Table 3).

**Table 3 table3:** Summary of secondary study hypotheses. Predicted relationships between intervention engagement, participant characteristics (sex and location), and clinical outcomes, including proposed mediating mechanisms, to be examined during quantitative analysis.

Variable	Description of hypothesis
Intervention group	Patients in the intervention group will show improvements in secondary health outcomes compared to patients in the control group (depression, anxiety, insomnia, liver health, and engagement in alcohol-related interventions and recovery activities).
Sex as a biological variable	Sex will moderate effects of Connections. Specifically, women receiving Connections will have greater improvements in outcomes than men.
Rural and/or nonrural locations	Living in rural versus nonrural locations will moderate effects of Connections. Specifically, those in rural areas will have greater improvements in outcomes than those in nonrural areas as defined by rural-urban continuum code.
Clinic type	Attendance at the ALD^a^ clinic offers attention to recovery and formal alcohol use disorder treatment as part of ALD treatment, potentially enhancing motivation and providing a foundation for deriving greater benefit from Connections. We hypothesize that those attending multidisciplinary ALD clinics will demonstrate greater benefit from Connections than those attending hepatology clinics.
Competence, relatedness, and autonomy as mediators	Effects of Connections on outcomes will be mediated by competence, relatedness, and autonomous motivation. We will test indirect effects of Connections on abstinence, indirect effects, and percent of the total effect mediated. Mediation analyses will only be undertaken if the main effect is statistically significant.
CHESS^b^ app use	Increased use of Connections will be associated with greater improvements in abstinence days. Greater use of Connections may reflect patients’ motivation for recovery and provide more opportunities to engage with recovery support.

^a^ALD: alcohol-associated liver disease.

^b^CHESS: Center for Health Enhancement Systems Studies.

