### Outcomes

#### Primary Outcomes

The primary outcome is patient alcohol use, which is measured using the patient-reported timeline follow-back (TLFB) calendar method and will be reported as percent days abstinent (Table 1) [38]. Abstinence, number of days drinking, and number of drinks per drinking day will be captured in the patient surveys. The TLFB will be administered once a month for 6 months to all enrolled participants using REDCap (Research Electronic Data Capture; Vanderbilt University), a password-protected electronic data capturing tool hosted at the University of Wisconsin-Madison [39].

**Table 1 table1:** Study outcomes, proposed outcome mediators, and outcome measurements used. Each dimension is measured by a well-validated instrument (Measure) and collected either from a patient survey, CHESS server logs, or from patient and/or staff interviews (Source) at different time points of the study (Timing). The selected measures allow for control of factors that may differ between patients and may impact alcohol use. The implementation process will be assessed using qualitative methods via semistructured patient and staff interviews.

Dimension			Measure		Source		Timing

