#### Power and Sample Size

The analysis assumes an intra-individual correlation coefficient of ρ=0.10 in alcohol abstinence days in the longitudinal mixed-effects model. With 7.5% loss to follow-up and a moderate effect size estimate of 0.3σ (using published effect sizes from prior CHESS platform studies) [50,51], the planned sample size of 298 participants (149 per randomization group) will have power ≥80% to detect a meaningful difference between randomization groups for the primary outcome of alcohol abstinent days.

The projected randomization of 298 participants is expected to be met due to the estimated recruitment pool of approximately 2361 patients with ALD across both sites. Of this total population, it is expected that approximately 690 patients will be part of the multidisciplinary ALD clinics. The randomization goal is less than 13% of the total estimated eligible population, which is likely a feasible recruitment rate based on prior studies led by members of the research team [52]. This feasibility is further supported by the recent pilot research recruitment rate of 11 out of 20 (55%) patients with ALD approached [53].

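### The primary analysis tests the group-by-time interaction and falls back on a group main effect if that fails, without saying which test decides the primary hypothesis or how the type I error is shared

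*Protocol article*

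**What the plan says.** The Primary Analysis section describes an intention-to-treat longitudinal linear mixed model, stratified by site and clinic type and adjusted for baseline abstinence and AUDIT-10. The decision rule follows: "The analyses will test a group-by-time interaction on the outcomes. If the interaction is not significant, a main group effect will be examined". The time points are then given: "The research team will construct a longitudinal model of our outcome measures at baseline and at 3 and 6 months after randomization". The primary outcome itself is collected more often: "The TLFB will be administered once a month for 6 months to all enrolled participants".

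Two later steps depend on the result. In the same section: "Secondary analyses (as-treated, per-protocol, CACE) will only be formally evaluated if the primary intention-to-treat outcome demonstrates a statistically significant effect". In the mediator row of Table 3: "Mediation analyses will only be undertaken if the main effect is statistically significant".

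Power and Sample Size justifies 298 participants by at least 80% power for a difference between randomization groups in abstinent days. It does not mention the interaction. Anticipated Findings states the primary hypothesis as more abstinent days in the intervention group. Neither these sections nor any other part of the article states an alpha, its sidedness, or a division of error between the two tests.

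**The concern.** A fixed testing sequence protects the error rate when it moves on after a success. This one moves on after a failure, so the second test is an additional chance to find something significant. The two contrasts are independent or nearly so, and their false-positive probabilities almost add.

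The two tests also answer different questions. The interaction asks whether the arms follow different trajectories. The main effect asks whether they differ in level. Only the second matches the stated hypothesis and the sample size justification, yet it is reached only when the first is non-significant. A significant interaction could reflect an early gain that is later lost, with no more abstinent days overall.

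At stake is the trial's main confirmatory claim, together with the as-treated, per-protocol, CACE and mediation analyses that open when that claim succeeds.

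**Working it through.** **Inputs from the article.** 149 per arm; 7.5% loss; effect 0.3 SD; ρ = 0.10 ("The analysis assumes an intra-individual correlation coefficient of ρ=0.10 in alcohol abstinence days"); model times baseline, 3 and 6 months. **Assumption, not in the article:** two-sided 5% per test.

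**1. The plan's own figure.** After loss, 149 × 0.925 = 137.8 per arm. Averaging m measurements multiplies the variance by (1 + (m − 1)ρ)/m, and power is Φ(0.3/√(2v/137.8) − 1.96).
- m = 2: v = 0.55, power 91.9%.
- m = 3: v = 0.40, power 97.6%.
- m = 6: v = 0.25, power 99.9%.
- m = 1: v = 1, power 70.2%.

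The stated power of at least 80% is therefore consistent with a repeated-measures group difference. It is a calculation for the main effect, not for the interaction.

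**2. Type I error of the two-step rule.** With no effect and independent tests at level a, the chance that at least one is significant is 1 − (1 − a)² = 2a − a².
- a = 5%: 1 − 0.95² = 9.75%.
- a = 2.5%: 1 − 0.975² = 4.94%.
- a = 1%: 1.99%.

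**3. Simulation under no effect, 5% per test.** Independence holds only approximately for some definitions of the main effect, so the rule was simulated with 2, 3 and 6 time points, under compound-symmetric, AR(1) and unequal-variance structures.

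| Definition of step 2 | Overall error |
|---|---|
| Main effect refitted without the interaction | 9.6–9.8% |
| Equal-weight average, equal variances | 9.6–9.8% |
| Equal-weight average, unequal variances | 8.0–9.7% |
| Finite-sample F and t tests, 138 per arm | 9.3–9.9% |
| 2-df interaction over baseline/3/6, then baseline-adjusted mean of 3 and 6 months (ρ = 0.1 and 0.6) | 9.0% and 8.2% |
| Last-visit contrast, most settings | 8.1–9.4% |
| Last-visit contrast, strongly unequal variances | 7.9% (3 times), 6.9% (2 times) |

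A single baseline-adjusted contrast, tested once, gave 5.0%.

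**4. Counting only favourable results.** Two-sided 5% tests leave 2.5% in the favourable direction. With a 1-df interaction the rule then gives 1 − 0.975² = 4.94% instead of 2.5%. The near-doubling is the same.

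**5. Cost of splitting alpha.** At two-sided 2.5% the critical value is 2.24. With 137.8 per arm, 0.3 SD and ρ = 0.10, main-effect power is about 87% for m = 2 (0.3/√(2 × 0.55/137.8) = 3.36; Φ(3.36 − 2.24)) and about 95% for m = 3.

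**The case against.** The strongest reply is that the plan never sets 5% for each test. That is correct. Alpha is commonly left to the SAP, which is not shown, and at 2.5% per test the same sequence would stay just under 5%. A reader might infer that the protocol itself fixes an 8 to 10% error rate. It does not, and the figure is conditional on the assumed level.

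Secondly, the main effect is only said to be examined, and the article does not state that either result counts as success. Treating both as routes to a positive trial is a natural reading, but it is a reading. It does not rescue the plan: if step 2 is not confirmatory, the interaction alone decides the trial, and the contrast behind the sample size and the hypothesis has no confirmatory test.

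Thirdly, a reader might infer that the gates contradict each other, because a significant interaction would leave the main effect untested and so close off mediation. The text does not establish this. It says what happens when the interaction fails, not that the main effect is barred otherwise, and it separately plans pairwise and time-specific comparisons. The main effect in Table 3 may simply mean the overall effect of the app. This is an ambiguity, not a proven contradiction.

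Finally, the exploratory labels under Moderator Analysis and Anticipated Findings cover moderators and secondary outcomes. They do not extend to the primary test.

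**Conclusion.** The concern holds in this form: the article fixes a two-step rule for the primary aim, moves to the second test on failure of the first, and says neither which test decides nor how the error is shared. If both tests are run at two-sided 5% and either can carry the claim, the type I error is about 9.75%, and roughly 8 to 10% in most settings. The lowest value found was 6.9%, for a last-visit contrast with strongly unequal variances, which is still above 5%. Apart from such settings, the error nearly doubles at any usual per-test level.

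The absence of an alpha is not itself the fault, since the SAP may supply one. The sequence is the fault, because the article fixes it. It should be settled before any unblinded analysis, since the confirmatory claim and the analyses gated on it rest on it.

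**What to change.** Preferred: name one primary contrast, the baseline-adjusted difference between arms in percent days abstinent, averaged over the post-randomization time points of the primary model. As the model is written, those are 3 and 6 months. Months 1 to 6 could be used instead if the model is aligned with the monthly TLFB, but that changes the stated model and should be declared as such. Test the contrast once at two-sided 5%. Keep the group-by-time term in the model, and report the interaction and the time-specific differences with confidence intervals as supportive.

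Alternative: keep both tests at two-sided 2.5% each, state that either one decides the primary hypothesis, and say how a significant interaction will be judged as benefit or harm. Overall error is then about 4.9%, and main-effect power stays at about 87% or more on the plan's repeated-measures inputs. That power depends on ρ = 0.10 and would be lower with a higher correlation.

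Under either option, state alpha and sidedness, and tie the as-treated, per-protocol, CACE and mediation gates to the declared primary result, replacing the reference to the main effect in Table 3.

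The cost is a wording change in the protocol or SAP. No participants or data are added. Enrolment stood at 144 of 298 in February 2026 and analysis is expected in 2028, so there is time to make the change before unblinded analysis.

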**Primary effectiveness outcomes**							
	Alcohol use	Timeline follow-back last 30 days (Abstinence, # of days drinking, # of drinks per drinking day)		Patient survey		Monthly	

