#### Secondary Outcomes

The secondary outcomes include quality of life, depression, anxiety, insomnia, health care usage, engagement with alcohol-targeted interventions, drinking motivations, alcohol risk assessment, and pain intensity and interference (Table 1). Quality of life will be measured using a 10-question Patient-Reported Outcomes Measurement Information System Global Health (PROMIS Global Health) [40], a questionnaire that evaluates and monitors physical, mental, and social health. Depression will be measured using the Patient Health Questionnaire (PHQ-8) [41], a tool used for screening, diagnosing, monitoring, and measuring the severity of depression. Patient anxiety will be measured using the General Anxiety Disorder-7 (GAD-7) [42], and insomnia will be measured using the insomnia severity index [43]. Engagement with alcohol-targeted interventions will be measured using participation in AUD treatment outside of the clinic, such as specialty outpatient treatment, peer support, or Alcohol or Other Drug Abuse treatment, as reported in the health care usage survey. Motivation for drinking will be measured using the Drinking Motives Questionnaire for Adults (DMQ-A) [44], and alcohol use risk will be measured with the Alcohol Use Disorders Identification Test (AUDIT-10) [45]. Pain intensity and functional interference will be measured using the Pain, Enjoyment, and General Activity 3-item scale (PEG) [46]. Survey measures will be administered at baseline, 3 months, and 6 months.

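### As written, the primary model is built at baseline, 3 and 6 months although the primary outcome is recorded in each of months 1 to 6, which costs precision and coverage but does not invalidate the test

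*Protocol article*

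**What the plan says.** Collection of the primary outcome is monthly. The Primary Outcomes section says "The TLFB will be administered once a month for 6 months to all enrolled participants", and Table 1 gives the instrument as "Timeline follow-back last 30 days" with monthly timing. The Monthly Surveys section repeats the 30-day recall, and Table 2 pays for each monthly survey.

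The secondary questionnaires follow another schedule: "Survey measures will be administered at baseline, 3 months, and 6 months" (Secondary Outcomes; Table 1 agrees, apart from AUDIT-10 at 0 and 6 months only).

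The Primary Analysis section then says: "The research team will construct a longitudinal model of our outcome measures at baseline and at 3 and 6 months after randomization". It adds a repeated-measures mixed model for incomplete data, with a choice of covariance structures, but names no time points for it. Group-by-time is tested first, and the main group effect is examined only if that interaction is not significant.

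The Power and Sample Size section assumes an "intra-individual correlation coefficient of ρ=0.10 in alcohol abstinence days in the longitudinal mixed-effects model" and does not say how many repeated measurements that model contains.

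**The concern.** The time points fixed for the primary model are those of the secondary measures, and no section says how the calendars from months 1, 2, 4 and 5 enter the primary test. Four consequences follow if the sentence is applied literally.

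- **Coverage.** The aim concerns days of abstinence over a six-month study. Relapse or recovery reported only in the other four months could not affect the estimate.
- **Precision.** Four of six follow-up records, already requested and paid for, would not contribute.
- **Missing data.** A participant who answers months 1, 2, 4 and 5 but misses 3 and 6 would contribute no post-baseline outcome. The article gives no frequency for this pattern, though its Challenges section expects lower response in some participants.
- **Analyst choice.** A monthly model and a 0/3/6-month model can both be argued from the text and may give different results. The as-treated, per-protocol and complier-average analyses depend on a significant primary result, and mediation depends on a significant main effect, so the choice carries forward.

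**Working it through.** **Inputs from the article.** Six monthly follow-up records; 30-day window; model at 0, 3 and 6 months; ρ = 0.10; 149 per arm; and "With 7.5% loss to follow-up and a moderate effect size estimate of 0.3σ". Adjustment for baseline abstinence is planned.

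**Assumptions of this check.** Two-sided α = 0.05 (the article gives neither level nor sidedness); compound symmetry; no missing data beyond the 7.5%; values at months 3 and 6 taken from one calendar each; an effect averaged over follow-up; ρ = 0.5 and 0.7 as illustrative alternatives.

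**Coverage.** 2 × 30 = 60 days, against 6 × 30 = 180.

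**The plan's power figure.** Evaluable n = 149 × 0.925 = 137.8 per arm. In units of σ², the mean of m equicorrelated records has variance f = (1 + (m − 1)ρ)/m. Adjusting for baseline with the same ρ gives f = (1 + (m − 1)ρ)/m − ρ². Power = Φ(0.3/√(2f/n) − 1.96).

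- m = 1: f = 1, power 70.2% (80.1% if one-sided).
- m = 2: f = 0.55, power 91.9%; adjusted f = 0.54, power 92.4%.
- m = 6: f = 0.25, power 99.9%; adjusted f = 0.24, power 99.9%.

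So power of at least 80% is reproduced as an inequality for two or six follow-up records. It does not reveal which number the authors used.

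**Standard error, months 3 and 6 relative to months 1–6.** The ratio is √(f for m = 2 / f for m = 6).

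| ρ | Unadjusted | Baseline-adjusted |
|---|---|---|
| 0.10 (plan) | √(0.55/0.25) = 1.483 | √(0.54/0.24) = 1.500 |
| 0.5 (assumed) | √(0.75/0.583) = 1.134 | √(0.50/0.333) = 1.225 |
| 0.7 (assumed) | √(0.85/0.75) = 1.065 | √(0.36/0.26) = 1.177 |

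At the plan's ρ the inflation is therefore 48–50%. At the assumed values it is 13% and 6% unadjusted, or 22% and 18% adjusted.

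**Group-by-time test, taken as a linear slope.** Under compound symmetry the ratio depends only on the spread of the time points. With baseline in the outcome vector, the sums of squares are 18 for 0, 3, 6 and 28 for 0–6, so √(28/18) = 1.247. With post-baseline points only they are 4.5 and 17.5, so √(17.5/4.5) = 1.972. Under AR(1) with baseline included, the inflation is 18% at ρ = 0.1 and falls to about 0% at 0.9. No single figure describes this test.

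**The case against.** The strongest reply is that the sentence is loose rather than exclusive. It speaks of outcome measures in general, on the schedule of the secondary questionnaires, and may have been written for them. The repeated-measures model that follows names no time points, so monthly calendars are not ruled out. A reader might infer that months 1, 2, 4 and 5 are deliberately and finally excluded; the article does not say that. What stands is that this sentence is the only statement of time points in the primary analysis, and nothing brings the other months in.

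A second reply is that the 3- and 6-month values could pool months 1–3 and 4–6. With complete data the average of those two quarters equals the six-month average, and neither days nor precision would be lost for the averaged effect. The text permits this but nowhere states it.

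Third, comparing arms at 3 and 6 months is a legitimate choice, and the Moderator Analysis also uses abstinence at 6 months. For a month-6 contrast with complete data, the extra months would add essentially nothing. A reader might infer that the trial is underpowered or its test invalid; the power check contradicts the first, and nothing in the article supports the second.

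Finally, a condensed article may leave windows and model detail to an analysis plan. That would answer silence. Here the article states time points, and they do not match its own collection schedule for the outcome.

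**Conclusion.** The mismatch is real, and no other section of the article resolves it. Its cost is a loss of efficiency and of follow-up coverage, together with an avoidable choice about which data form the primary result.

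Only the 48–50% inflation of the standard error rests on the plan's own correlation. Even that requires compound symmetry, single 30-day windows and a time-averaged effect. The smaller figures rest on assumed correlations, so a reader should not take any range of losses as following from the article alone. Because the power claim survives, this is a worthwhile improvement at little cost rather than a defect that must be repaired for the trial to be valid.

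**What to change.** 1. In the Primary Analysis section, state that the primary model uses all six monthly TLFB records, adjusted for baseline percent days abstinent, AUDIT-10, site and clinic type.
2. Name the group effect averaged over months 1–6 as the primary contrast. Adding months without doing so would leave an arm-by-month interaction with 5 degrees of freedom as the first test, so the sentence that orders the two tests needs rewording as well.
3. Confine the 0/3/6-month structure to the quarterly secondary measures. If 3 and 6 months are intended for the primary outcome, justify that and say whether each value comes from one calendar or from three pooled months.
4. In Power and Sample Size, give the number of repeated measurements and the significance level behind the stated power.

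No new data are needed. The cost is the wording and some extra modelling work. Recruitment is still under way (144 of 298 enrolled by February 26, 2026), so this can be settled before the analysis planned for 2028.
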